#### Financial incentives encouraging data return

To recognise time taken for study participation, participants will receive up to £50 in ‘Love to Shop’ gift cards, which cannot be redeemed for tobacco or alcohol. To receive maximum remuneration, participants will need to submit all adherence app data; they will receive 50p for each daily app report, and an additional £1.50 for supplying a continuous full week’s reports, plus an additional £5 if they report for all 28 days after their QD (maximum total £25). Further gift cards will be given to women if they provide requested questionnaire data and validation saliva samples.

#### Fidelity assessment (pilot phase only)

We will audio-record all initial intervention group consultations, selecting a random sample for further scrutiny. Two researchers will listen to the selected audio recordings, independently rating the completeness of intervention delivery against a fidelity checklist that lists key components of the BMN intervention, and inter-rater reliability between researchers will be determined. We will store recordings on a secure University of Nottingham server for a maximum of 7 years.

#### Data management

Each participant will be assigned a unique study identification number allocated at consent to identify their data and biological samples. Personal identifiers (name, email address and phone number) will be stored in a password-protected computer database accessible only by the researchers. Data will be entered into a REDCap database where possible, but paper case report forms may be used as source data and entered by researchers into the database. Information submitted by participants via the NicUse app is stored as pseudonymised data on the Amazon cloud.

All electronic data will be securely stored at the University of Nottingham for 15 years after which it will be destroyed. Data management will be led by the York Trials Unit, with the support of the Trial Manager at the University of Nottingham as detailed in the Data Management Plan.

The Trial Management Group is responsible for the day-to-day running of the trial, meeting regularly and is supported and reportedby the Trial Steering Committee (TSC) (see online supplemental file).

#### Saliva samples

Saliva samples will be collected by researchers or by participants and sent by post directly to ACM labs for storage and analysis at the end of the trial. The laboratory will quantify salivary cotinine concentrations and the presence or absence anabasine using a quantitative enzyme immunoassay technique. Once the analysis has been completed, the saliva samples will be destroyed in accordance with the Human Tissue Act 2004.

### Outcomes

#### Primary outcome

Reported smoking abstinence in late pregnancy or around childbirth with appropriate biochemical validation.

#### Secondary outcomes

Reported smoking abstinence at *both* 28 days and in late pregnancy or at childbirth, with and without appropriate biochemical validation in late pregnancy.Reported smoking abstinence for 24 hours and 7 days at 28 days.Reported number of days NRT is used in the first 28 days following a QD.Reported mean daily nicotine dose in the first 7 days of quitting (‘intensity’ of NRT use).Engagement with BMN intervention components.

#### Pilot phase outcomes

Urges to smoke, ‘cravings’, and tobacco withdrawal symptoms.NRT concerns and necessity beliefs at baseline and Day 28.Fidelity of intervention delivery as measured against fidelity checklist.

#### Other outcomes

Saliva cotinine concentration.Number of days NRT use between a QD and the end of pregnancy.Exhaled CO concentration.Birth weight.Low birth weight (<2500 g).Gestational age at birth.Maternal or fetal death (stillbirth or miscarriage).Caesarean section delivery.Neonatal intensive care admission.Congenital anomaly.

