##### Counselling

Participants are asked to complete a short questionnaire to assess their concerns and necessity beliefs regarding the use of NRT in pregnancy^29^; the latter are views on how worthwhile NRT might be to participants. The number of counselling sessions mirrors that of UC, but the content addresses individual concerns and beliefs about the safety of nicotine and the efficacy of nicotine replacement products. The first counselling session is on average 10 min longer than those delivered in UC, is delivered via video call where possible and addresses individual concerns and beliefs about the safety of nicotine. To ensure advice is as personalised as possible, SSPs respond to key concerns and necessary beliefs recorded on questionnaires. Participants are advised, if needed, to use a patch and short-acting NRT preparation until childbirth and during brief lapses to smoking (of up to 14 days), provided they still try to quit. To avoid morning cravings, 24-hour NRT patches may be left on overnight, and support is aimed at maintaining adherence to NRT. Follow-up calls are mainly by telephone; these again focus on addressing concerns about nicotine, using sufficient NRT and not stopping this during brief smoking lapses, in addition to the UC advice.

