### Data collection

Table 1 shows all participant data collection at time points outlined below and indicates how intervention delivery fits with this. Figure 1 is a study flow diagram. We indicate which measures will be used for research purposes in the pilot only.

**Table 1 T1:** Schedule of data collection and intervention delivery time points

Data collected	Time point								
	Pre-baseline (consent)	Baseline*	Pre-Quit Date	Days 1–3	Day 7	Day 14	Day 21	Day 28	Delivery (Week 36 gestation)
Informed consent	X†								
Smoking status/ CPD/use of ecigs		X			P‡			X	X
Cravings & tobacco withdrawal		P			P			P	
NRT concerns & necessity beliefs		P						P	
Saliva samples		P			P				X
Exhaled CO		X							X
NRT adherence data					P			X	X
Reported engagement with intervention								X	
NicUse app data collection									
Medical records data									X
Intervention Delivery (both trial arms)									
Counselling from SSPs offered			X	X	X	X	X	X	
NRT dispatch			X		X	X	X	X	

*Randomisation follows baseline data collection

†X=data collected in both pilot and full trial phase

‡P=data collected only in the pilot phase

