#### Baseline

We will ask participants about demographics, gestation, estimated date of delivery, partner smoking status, whether they smoked in previous pregnancies, nicotine dependence,^30^ current and pre-pregnancy smoking behaviours, experience using NRT, smoking beliefs, urges to smoke (cravings) and tobacco withdrawal symptoms.^31^ Where possible, those recruited in person will also provide an expired air CO reading at baseline. Researchers will also help participants to instal the ‘NicUse’ smartphone app from Google Play and Apple Store,^32^ a bespoke app developed for SNAP2 on which applicants record daily smoking, e-cigarette and NRT use (see below) during the 28-day intervention period. We will seek contact details for participants’ GPs and check with them if there is any reason why a participant should not be enrolled.

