#### 36 weeks of gestation or delivery (if earlier)

We will ask participants about smoking, adherence to NRT since 28-day follow-up and use of NHS stop smoking support. We will send non-responders a direct-reply text message asking about smoking in the previous 7 days.

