#### Routine data collected from medical records

NHS hospitals collect smoking status and exhaled CO from every woman from week 36 of gestation onwards, and we will collect these data from NHS records. We will also extract maternal and fetal pregnancy outcome data from medical records. In NHS hospitals, research staff will collect these data; otherwise, the research team contact relevant NHS staff to ask for this information. Where birth outcome data cannot be obtained from records, using methods outlined above, we will ask participants to provide birth weight, gestation at delivery, whether they underwent caesarean section or the baby was admitted to special care or had any congenital abnormality and whether they were a smoker or non-smoker at delivery.

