#### Validation of smoking abstinence

For participants who report 7-day smoking abstinence at 36 weeks or later, we will collect saliva samples as they attend hospital, at home visits or postally (see above). Before giving samples, participants will be asked about any recent smoking, vaping or NRT use.

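### The outcome counting NRT days to the end of pregnancy is cut off at the late-pregnancy questionnaire for women who deliver after it

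*Protocol article*

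**What the plan says.** The protocol article, under Other outcomes, lists "Number of days NRT use between a QD and the end of pregnancy", where QD is the quit date. The sources of NRT data are described in separate sections:

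- **Baseline.** The NicUse app is where participants "record daily smoking, e-cigarette and NRT use (see below) during the 28-day intervention period".
- **Day 28 after the QD.** A questionnaire covers the previous 28 days. Women who supply no data on smoking or NRT by app or questionnaire get a text asking about NRT use since the QD.
- **36 weeks of gestation or delivery (if earlier).** The last scheduled questionnaire is described thus: "We will ask participants about smoking, adherence to NRT since 28-day follow-up and use of NHS stop smoking support". Non-responders get a text that asks only about smoking in the previous 7 days.
- **Validation of smoking abstinence.** "For participants who report 7-day smoking abstinence at 36 weeks or later, we will collect saliva samples as they attend hospital", or at home or by post. Before the sample they are asked about recent smoking, vaping or NRT use.
- **Routine data collected from medical records.** Where records cannot supply birth outcomes, women are asked for a list of items that ends with "whether they were a smoker or non-smoker at delivery". NRT is not on the list.

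Table 1 marks NRT adherence data in a last column headed "Delivery (Week 36 gestation" (closing bracket omitted here). Under Counselling, BMN participants are advised, if needed, "to use a patch and short-acting NRT preparation until childbirth". Under Procedures for missing, unused and spurious data, a missing NRT response is taken as no use in the period concerned, with sensitivity analyses under other assumptions.

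**The concern.** The outcome claims a window that closes at birth, while the last count of NRT days closes at the date of the late-pregnancy questionnaire. Most women who answer around 36 weeks will still be pregnant. Their later NRT days are never asked about, whereas a woman who delivers before 36 weeks is covered in full. The same label then means different periods depending on gestation at birth, which is itself one of the trial's outcomes.

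At stake is the description of how long women used NRT. A total reported as running to the end of pregnancy would be read as a whole-pregnancy count that was not collected. The uncounted weeks also lie where the two arms' described advice differs, because advice to continue until childbirth appears only in the BMN section.

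The 36-week fallback text creates a related gap. It has no NRT item, so a woman who replies only that way is treated as having used no NRT at any time after Day 28.

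**Working it through.** The article gives no figure for this outcome that could be reproduced, so the check has three parts.

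**1. Which source counts NRT days, and up to when**

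| Source | NRT period covered | Count of days? | Reaches birth if birth follows the 36-week questionnaire? |
|---|---|---|---|
| NicUse app | 28-day intervention period | Yes | No |
| Day 28 questionnaire or text | QD to Day 28 | Questionnaire yes; text asks about use since the QD | No |
| Late-pregnancy questionnaire | Day 28 follow-up to the date answered | Can supply one | No |
| Question before saliva sample | Recent use, in reported abstainers only | Not described as one | No |
| Contact when birth records fail | NRT not listed | No | No |

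No row covers the stretch from the questionnaire to a later birth.

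**2. Length of the uncounted stretch**

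Inputs: the questionnaire is answered at 36+0 (assumption). Birth week B and quit-date week Q are also assumptions, taken over a range. The upper end of Q follows from the inclusion criteria: entry before 25 weeks, so at most 24+6, plus a quit attempt within 14 days, gives 26+6, rounded to 27.

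- Uncounted days = 7 × max(0, B − 36)
- Full window = 7 × (B − Q)
- Share = uncounted days ÷ full window

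| QD week | Birth at 37 | Birth at 40 | Birth at 42 |
|---|---|---|---|
| 8 | 7/203 = 3% | 28/224 = 12.5% | 42/238 = 18% |
| 12 | 7/175 = 4% | 28/196 = 14% | 42/210 = 20% |
| 20 | 7/119 = 6% | 28/140 = 20% | 42/154 = 27% |
| 27 | 7/70 = 10% | 28/91 = 31% | 42/105 = 40% |

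For birth at 35 weeks the uncounted stretch is 0. The gap is thus 7 to 42 days for births at 37 to 42 weeks, or 3% to 40% of the window over this grid. These are days without observation. They are days of lost NRT use only for women still using it.

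**3. Women who reply at 36 weeks only by text**

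Days from Day 28 to 36+0 that are set to non-use = 7 × (36 − Q) − 28:

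- Q = 12: 168 − 28 = 140 days
- Q = 20: 112 − 28 = 84 days
- Q = 27: 63 − 28 = 35 days

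The article does not say how many women reply only this way.

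**The case against.** Several points on the other side have force.

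- **A reader might infer that the outcome cannot be measured at all.** The article does not support that. App, Day 28 questionnaire and late-pregnancy questionnaire together cover the quit date to about 36 weeks for women who respond, and the whole window for those who deliver earlier. The outcome is truncated.
- **A reader might infer that NRT is never asked about after the 36-week questionnaire.** It can be, before a saliva sample taken at 36 weeks or later. That question reaches only women reporting abstinence and concerns recent use, so it does not supply the missing count.
- **The timing is looser than 36+0.** The abstract has the late assessment measured from 36 weeks, Table 1 names both delivery and week 36, and the Follow-up section allows reminders, calls and posted forms. Later answers shorten the gap but make the window more variable.
- **A reader might conclude that the between-arm difference is understated.** This is a plausible direction only. The BMN advice is qualified by need, trial support lasts 28 days with local usual care afterwards in both arms, and the introduction reports that only 7% to 30% completed NRT courses in pregnancy trials. The article gives no late-pregnancy NRT use for either arm.
- **The outcome ranks low.** This stands, although it is not certain that it will only be described. Assessment of efficacy lists adherence to NRT among measures compared by model and says the remaining outcomes are summarised descriptively, without placing this one.
- **The full protocol or SAP may define the end of the window.** If so, only the label needs aligning. Neither document can recover days that nobody was asked about.

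**Conclusion.** The mismatch is real and minor in consequence. As the article describes data collection, the outcome named to the end of pregnancy is in fact a count to the late-pregnancy questionnaire for women who deliver after it, and a count to delivery for those who deliver sooner. The size in part 2 of the working rests on an answer at exactly 36+0 and on assumed quit-date and birth weeks. The upper percentages belong to late quit dates combined with late births and are not typical values.

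Any excess loss in the BMN arm would pull this comparison towards no difference, but its size cannot be obtained from the article and it should not be stated as established. The text-only gap is separate. It can span more days per woman, its frequency is unknown, and the planned sensitivity analyses address it only in part. The primary outcome and the listed secondary NRT outcomes, which cover the first 28 and the first 7 days, are untouched.

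**What to change.** 1. Redefine the outcome as days of NRT use from the QD to the date of the final questionnaire (36 weeks, or delivery if earlier). Report it with the length of the observed period by arm, since that length varies with the quit date, the response date and gestation at birth.
2. Reconcile the Table 1 column heading with the follow-up section, so that both state the same time point.
3. Add an NRT-use item to the 36-week fallback text, as the Day 28 text already has. Record the date it was introduced. Women followed up before then stay under the non-use rule and its sensitivity analyses.

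Steps 1 and 2 cost only wording, at the price of a narrower claim. Step 3 costs one text item.

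Keeping the present label and asking every woman after birth about NRT since the questionnaire is a weaker choice. Recruitment began in June 2021, so women who have already delivered would be missed and two definitions mixed. It would also need a new contact, because women are asked for birth data only where records fall short.

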### Sample size and justification

#### Design changes

Originally, we planned SNAP2 as an RCT to test the extent to which BMN did or did not increase adherence to NRT; adherence to NRT was intended as the primary outcome and smoking outcomes as secondary. If study findings gave a sufficiently positive ‘signal’ for an effect on NRT adherence, we planned a second RCT to test whether BMN had positive effects on smoking cessation. However, due to the COVID-19 pandemic and NHS service provision changes, the funder agreed that BMN efficacy for smoking abstinence would be better investigated instead of simply using a measure of smoking behaviour as the trial primary outcome and increasing the SNAP2 sample size. This was dependent on a successful pilot phase of the trial in which (a) BMN demonstrated a sufficiently large ‘signal’ that impacts the adherence to NRT and (b) explanatory trial outcome data were collected before being discontinued in the more pragmatic ‘full’ trial. Below we detail how, in the SNAP2 pilot phase, the impact of BNM on adherence to NRT was assessed, and progression decided on.

#### Assessment of BMN’s potential effect on NRT adherence’

For the original SNAP2 RCT, we defined a clinically important effect as BMN increasing NRT use by 21%. Data from a previous study indicated that if the control group was offered NRT for 28 days, they were likely to use this on a mean of 7 days,^34^ so a 21% increase represented an extra 1–2 days of NRT use.

We used a one-sided CI approach^35^ to assess whether or not the pilot phase SNAP2 trial ‘signal’ for the impact of BMN on NRT adherence was consistent with assumed effects. Using a CI approach, we calculated that for the checkpoint analysis to produce an upper limit of a one-sided 80% or 90% CI that excludes the estimate of effect, assuming the treatment estimate from the checkpoint assessment was zero or less would require 34 or 54 in the analysis. A trial statistician estimated BMN efficacy using data from 49 participants followed up to the primary outcome point. The point estimate and the upper confidence limit (whether 80% or 90%) were greater than the pre-specified clinically relevant effect size of 1.21. The funder deemed this sufficient demonstration of potential efficacy for the pilot to progress to a full trial.

#### Full trial sample size estimate

To determine the sample size for the full trial, we assume a control group quit rate of 10%, consistent with similar UK studies,^34 36 37^ and seek to detect an absolute increase in the risk of abstinence of 6% (corresponding to a risk ratio (RR) of 1.6). We think this is a reasonable effect size to seek as all previous trials of NRT used by pregnant women tested the use of only one NRT product and these show a relatively weak, imprecise effect (RR 1.37, 95% CI 1.08 to 1.74),^13^ with smaller point estimates seen in the least biased studies (RR 1.21, 95% CI 0.95 to 1.55).^13^ However, in non-pregnant smokers where adherence to NRT is much stronger, depending on the type of NRT used, Cochrane review point estimates for NRT efficacy range between 1.49 (for gum) and 2.02 (inhaler),^38^ and dual NRT (patch+fast acting) is more effective than single product use, with an OR for abstinence with NRT of 1.25 (dual vs single product NRT use).^12^ We aim to recruit 1320 participants, providing a minimum of 90% power for a two-sided test of size 5%, assuming the control group’s quit rate is at least 10%.

### Analyses

Statistical analysis will be conducted when the trial ends using Stata/MP v18 or later unless specified otherwise. All analysis software used including any community-contributed software will be explicitly cited in any publication of the trial results. Significance tests will be two-sided at the 5% level unless specified otherwise. Point estimates will be presented with their associated 95% CIs. Full analyses will be detailed in a statistical analysis plan (SAP), finalised before the end of data collection, and which will be reviewed by the TSC. A CONSORT flow diagram will be provided to display the flow of participants through the study. Baseline data will be summarised descriptively by group, for all randomised and for all those who are included in the primary analysis. No formal statistical comparisons of group differences at baseline will be conducted. Continuous measures will be reported as means and SD, while categorical data will be reported as counts and percentages.

#### Assessment of efficacy

The primary efficacy endpoint is reported abstinence in late pregnancy or around childbirth, validated by appropriate biochemical measures (binary—abstinent or non-abstinent). The primary analysis model will include all randomised participants as part of the groups to which they were allocated, with any missing primary endpoints imputed as being non-abstinent. We will compare abstinence between treatment groups using logistic regression, with fixed effects of the treatment group, gestation at baseline (the stratification factor) and other predictive baseline covariates (pre-specified in the SAP). In addition to the point and interval estimate of the OR for allocation, we will use the fitted model to obtain estimates of treatment effects on both the relative risk and risk difference scales. Binary secondary outcomes (eg, other abstinence outcomes) will be analysed in a broadly similar manner to the analysis of the primary outcome. Secondary outcomes including adherence to NRT, NRT adherence intensity, cotinine (smoking exposure), necessities/concerns and birth outcomes will be compared between arms using appropriate generalised linear models. All other outcomes will be summarised descriptively by a randomised arm. If the relevant data are sufficiently complete, we will perform exploratory analyses to decompose the total effect of allocation on the primary outcome into indirect effects (ie, those mediated by improved NRT adherence/usage) and direct effects (ie, those not mediated by improved NRT adherence/usage).

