## Introduction

Smoking in pregnancy is still a prevalent public health issue worldwide. For example in the UK, around 7.5% of UK women smoke during childbirth.^1^ Smoking in pregnancy is associated with preventable negative outcomes for both women and babies, and women who stop smoking during pregnancy are less likely to have premature or low-birth-weight infants.^2^ Compared with mothers who do not smoke, those who continue smoking in pregnancy have heightened risks of placental abruption, miscarriage, stillbirth and ectopic pregnancy.^3^ Children born to parents who smoke are more likely to start smoking themselves,^4^ and tobacco smoking is a major risk factor for six of the eight leading causes of death worldwide.^5^

Pregnancy is probably a life event that most motivates people to try to quit smoking; around 50% of women who smoke stop during gestation; and many others try but fail.^6^ A key reason is that nicotine withdrawal symptoms and smoking urges experienced while trying to stop smoking are difficult to tolerate. Nicotine replacement therapy (NRT) provides nicotine without exposing users to toxins like tar, cyanide and carbon monoxide (CO) and, thereby, safely helps ameliorate withdrawal and smoking urges. In the UK, the National Institute for Health and Care Excellence recommended NRT use in pregnancy since 2010^7 8^ and is now a central component of routine clinical practice.^9–11^ However, although NRT is effective in general,^12^ it appears to work less well in pregnancy,^13^ probably because pregnant women do not use it consistently, long enough or in sufficient doses. In trials enrolling pregnant smokers, only 7% to 30% finished courses of NRT,^13^ and of pregnant smokers prescribed NRT by UK general practitioners (GPs), only 30% were supplied it for longer than 2 weeks,^11^ and such short NRT courses are ineffective. In contrast, non-pregnant smokers enrolled in smoking cessation trials report up to 94% adherence levels.^14^

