#### Other objectives (pilot phase only)

To compare biochemically measured nicotine exposure before and after exposure to BMN intervention

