#### Day 7 after the QD (pilot phase only)

We were asked if a quit attempt was made; if any NRT had been used since the QD and, if so, how many days, which types; and if short-acting NRT is used, how many lozenges, cartridges or sprays were used. We also asked about current smoking, e-cigarette use, urges to smoke (cravings) and tobacco withdrawal symptoms. As soon as possible after Day 7, saliva samples (see above) were collected from participants. After the pilot, we discontinued data collection at this time point, as this information was only required for pilot phase outcomes.

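### Cotinine is labelled smoking exposure and tested between arms, although it also reflects the NRT that the intervention is designed to increase

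*Protocol article*

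**What the plan says.** The analysis commitment is in Assessment of efficacy: "Secondary outcomes including adherence to NRT, NRT adherence intensity, cotinine (smoking exposure), necessities/concerns and birth outcomes will be compared between arms", by means of generalised linear models. That sentence gives no time point, no population and no handling of NRT use.

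Other parts of the article bear on what cotinine can mean here:

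- **Introduction:** "Nicotine replacement therapy (NRT) provides nicotine without exposing users to toxins", with carbon monoxide named among those toxins.
- **Other objectives (pilot phase only):** "To compare biochemically measured nicotine exposure before and after exposure to BMN intervention". Here the biochemical measure is nicotine exposure, not smoking exposure.
- **Intervention, Counselling:** "Participants are advised, if needed, to use a patch and short-acting NRT preparation until childbirth". The same advice extends to short lapses into smoking. Under usual care (Before QD), NRT is to be used only when not smoking.
- **Validation of smoking abstinence:** "For participants who report 7-day smoking abstinence at 36 weeks or later, we will collect saliva samples".
- **Day 7 after the QD (pilot phase only):** "As soon as possible after Day 7, saliva samples (see above) were collected from participants". Table 1 shows saliva at baseline and Day 7 in the pilot only, and in late pregnancy in both phases.
- **Saliva samples:** the laboratory reports anabasine as present or absent, in addition to cotinine.
- **Outcomes:** saliva cotinine and exhaled CO both appear under Other outcomes, and neither appears under Secondary outcomes.

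**The concern.** In most cessation trials cotinine is a fair proxy for smoking. Here the arms are meant to differ in NRT use, which is the other main source of nicotine. The better BMN works on adherence, the more it raises cotinine at any given level of smoking. A formal test labelled smoking exposure could then show more apparent exposure in the arm that smokes less, or hide a real reduction.

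A second problem depends on which sample is used. Late-pregnancy saliva comes from women who report 7-day abstinence. Abstinence is what BMN is meant to change, so a comparison within that group is not a comparison of the groups as randomised. Among those who truly abstain, no cotinine comes from their own smoking, so a difference between arms cannot be an effect on it.

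**Working it through.** **1. The plan's own figure.** The article states no number for cotinine. The only figure to reproduce is the sample size (Full trial sample size estimate): 10% v 16%, 90% power, two-sided 5%, 1320 in total. No allocation ratio is stated, so I assume 1:1. With pooled variance and no continuity correction:

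n per arm = [1.960·√(2·0.13·0.87) + 1.282·√(0.10·0.90 + 0.16·0.84)]² / 0.06² = 659, or 1318 in total.

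Power at 660 per arm is 90.1%. The plan's figure is reproduced.

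**2. Size of the late-pregnancy group.** Validated abstainers at the planning rates are 660 × 0.10 = 66 under usual care and 660 × 0.16 = 105.6, about 106, under BMN. Together that is (66 + 105.6)/1320 = 13% of the trial. These are not counts of saliva givers. Women who report abstinence and fail validation add to them, unreturned samples subtract, and the article gives neither number.

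**3. Direction check.** All levels and rates below are assumptions, because the article gives none. A smoker has cotinine 100, an abstainer on NRT has L = 30, 50 or 80, and an abstainer without NRT has 0. Let u be the proportion using NRT.

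*Case A, true abstainers only.* Mean = L·u.

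| NRT use, usual care v BMN | L = 30 | L = 50 | L = 80 |
|---|---|---|---|
| 20% v 40% | 6 v 12 (+6) | 10 v 20 (+10) | 16 v 32 (+16) |
| 30% v 30% | 9 v 9 (0) | 15 v 15 (0) | 24 v 24 (0) |

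Nobody smokes in either arm, so the whole difference is NRT.

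*Case B, women reporting abstinence, some of whom smoke.* Let m be the proportion who smoke: 30% under usual care and 20% under BMN, so BMN is better. Mean = 100·m + (1 − m)·L·u. Differences are BMN minus usual care.

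| NRT use, usual care v BMN | L = 30 | L = 50 | L = 80 |
|---|---|---|---|
| 10% v 40% | -2.5 | +2.5 | +10.0 |
| 20% v 40% | -4.6 | -1.0 | +4.4 |

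For example, at L = 50 in the first row: usual care 30 + 0.7 × 5 = 33.5, BMN 20 + 0.8 × 20 = 36.0.

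*Case C, all women at a Day 7 type of visit.* Abstinence q is 20% v 26% and NRT use is 30% v 60%. NRT adds a = 0 to 40 units in women who still smoke. Mean = q·L·u + (1 − q)·(100 + a·u).

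- L = 30, a = 0: usual care 1.8 + 80 = 81.8; BMN 4.7 + 74 = 78.7; difference -3.1.
- L = 80, a = 40: usual care 4.8 + 89.6 = 94.4; BMN 12.5 + 91.8 = 104.2; difference +9.8.

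In cases B and C, BMN has less smoking throughout, yet the cotinine difference takes either sign. Case C shows that this does not depend on selecting abstainers.

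**The case against.** The strongest reply is that Assessment of efficacy does not name the sample. The same sentence lists necessity and concerns beliefs, which are pilot-only, and the only biochemical-exposure objective is also pilot-only. A natural reading is that cotinine is compared at pilot Day 7, where saliva was sought in both arms whatever the smoking status. This stands. A reader might infer that the planned comparison is certainly restricted to self-reported abstainers, but the article does not say so. Time point and population may properly be left to the SAP.

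Next, the team plainly knows that NRT supplies nicotine. Recent smoking, vaping and NRT use are asked about before sampling, anabasine is assayed, and CO is collected. That is true, but the section specifying the test names none of these and attaches the smoking label to cotinine.

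The sign reversal rests on assumed inputs. Trial-delivered support ends at 28 days, NRT until childbirth is advised only if needed, and the article gives no between-arm difference in NRT use at 36 weeks. All of this stands, so a reversal is possible but not shown.

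It is also tempting to read the pilot objective's before-and-after wording as a planned paired analysis. It is a one-line objective, and the analysis section speaks of arms.

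Finally, the routine-data section says "NHS hospitals collect smoking status and exhaled CO from every woman from week 36 of gestation onwards". That describes NHS practice and does not guarantee a reading for every participant.

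**Conclusion.** The concern holds for the label and for the inference it invites: a between-arm difference in cotinine cannot be read as a difference in smoking, and it could go in the wrong direction. This applies to whichever sample is used. It rests on cotinine being a nicotine marker. The article does not say so outright, but that fits its own description of the pilot measure as nicotine exposure and its statement that NRT supplies nicotine.

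The selection problem is conditional. It arises only if late-pregnancy saliva is what is compared.

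The tier is also inconsistent: cotinine is listed under Other outcomes but is called secondary and formally compared in the analysis section.

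A reader might infer that the primary result is compromised. The documents do not support that. The primary outcome is binary abstinence with appropriate validation, CO and anabasine are available, and validation rules may be in the SAP. This is an inexpensive correction to a lower-tier outcome that should be made before results are interpreted.

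**What to change.** - **Relabel** cotinine as total nicotine exposure wherever it is named as an outcome.
- **Formal comparison:** make any between-arm test on the pilot Day 7 samples, adjusted for baseline cotinine. The pilot recruited 264 women, so that is the ceiling before unreturned samples.
- **Late pregnancy:** report cotinine descriptively by arm among sample givers, with their number in each arm.
- **Smoking exposure:** base any statement on markers not raised by NRT that the trial already collects. For late pregnancy use exhaled CO from NHS records, with completeness by arm. Anabasine can also be used, but in late pregnancy it comes from the same saliva and carries the same restriction to reported abstainers.
- **Tier:** reconcile Other outcomes with Assessment of efficacy, so that cotinine has one tier and one stated type of analysis.

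The cost is wording in the protocol and SAP, plus one comparison that becomes descriptive. No new data are needed, and the primary outcome and sample size do not change. The Analyses section says the SAP is to be finalised before data collection ends, so the change should be made by then.
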